Aim: To explore the safety, tolerability, and initial efficacy of psilocybin administered with psychological support compared to Treatment as Usual (TAU) in adolescents and young adults aged 16-35 with anorexia nervosa (AN).

Primary Objective: To assess the safety and tolerability of psilocybin 25 mg in this population.

Secondary Objectives: To evaluate the efficacy of psilocybin with psychological support in reducing AN symptom compared to TAU, investigate potential mechanisms of action through self-report questionnaires, neuroimaging and BDNF analysis, and conduct qualitative analysis of subjective experiences.

Trial Design: Open, randomized controlled trial with two arms: (1) two doses of psilocybin (25 mg) with psychological support with one month apart and alongside treatment as usual, and (2) Treatment as Usual (TAU).

Trial Population: Adolescents and young adults aged 16-35 diagnosed with anorexia nervosa.

Number of Subjects: 40 participants (20 per group).

Inclusion Criteria: Diagnosed with AN per DSM-5, aged 16-35, BMI >16, who have experienced at least one period of weight gain followed by weight loss.

Exclusion Criteria: Psychosis, bipolar disorder, substance use disorder, contraindicated medications, severe medical conditions, or metal contraindications for MRI.

Intervention: Two doses of 25 mg psilocybin with psychological support, or TAU. Psilocybin sessions will be accompanied by preparatory and integration sessions.

Investigational Medicinal Product Dosage Administration: Psilocybin 25 mg administered orally during supervised sessions.

Ethical Considerations/Benefit-Risk: Comprehensive safety monitoring, support during sessions, and procedures in place for managing any adverse events. First 25 participants included above 18 years of age, followed by 15 patients between 16-17 years of age. Safety review committee after first 10 psilocybin dosing sessions to review adverse events and protocol adherence. Literature on psilocybin clinical trials report low risk for adverse events and large gap in treatment options for patients with relapse in anorexia nervosa.

Planned Duration of the Trial: Q3 2025 – Q2 2027.

2. Background and Rationale

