5.1 Overall Trial Design

- A Phase IIa, open-label, randomized controlled trial with two arms:

1. Active treatment arm; Two dosing sessions with psilocybin 25mg with psychological support alongside TAU.

2. Active comparator control arm; TAU only.

TAU includes specialized care offered in an eating disorder unit in Region Skåne, Sweden. If the active treatment arm is determined to be safe, tolerable, and preliminarily effective during the follow-up assessment, participants in the control group will have the option to switch to the active treatment while maintaining their usual specialized care.

This design minimizes ethical concerns regarding withholding a potentially effective treatment.

Participants will be randomly assigned (1:1) to either the intervention or control group.

Block randomization stratified by age group (16–17 and 18–35 years) will ensure balanced representation.

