10.2 Statistical Analyses

This will be an open label, two-arm, active comparator (TAU; treatment as usual), , randomized controlled, between- and within-subjects, design in up to 40 completing patients meeting DSM-5 criteria for eating disorders. The patients will be randomly allocated to the psilocybin treatment-arm. The study analyses will enable comparison of efficacy between psilocybin-treatment and treatment as usual, as well as longitudinal within-patient efficacies.

- Primary Baseline Analyses:
  The primary analyses will involve descriptive statistics for demographic and baseline characteristics, ensuring comparability across groups, and control for follow-up measurements.
- Primary Endpoints analysis
- We will analyse differences in the number of participants and severity experiencing AE/SAE between the groups standardized forms for AE/SAE capturing: Event description, Start and end dates, Severity (e.g., mild, moderate, severe), Relatedness to intervention (assessed by safety review committee), Action taken.

The primary statistical methods will be:

- Descriptive Frequencies and Percentages.
- Comparing Proportions (Most Common for "Incidence") (Chi-squared test (or Fisher's Exact Test): Fisher's exact test is preferred for small cell counts (<5).
- Risk Ratio (RR) or Odds Ratio (OR) with Confidence Intervals: Report these measures of effect size to quantify the magnitude and precision of the difference between groups. An RR > 1 would indicate a higher risk in the intervention group.
- Comparing Severity and Relatedness is assessed with Mann-Whitney U test or Student t-test to compare severity distributions between groups.
- Secondary Endpoints:
  For secondary endpoints (e.g., changes in fMRI connectivity, BDNF, rating scales), group comparisons, including t-test, ANOVA, and Repeated Measures ANOVA will be utilized. When controlling for variables such as individual differences, ANCOVA or MANCOVA will be utilized. Principal component analysis (PCA) or independent component analysis (ICA) may be applied to identify patterns in fMRI data. Task-based fMRI data will be analysed using univariate models to investigate treatment effects in syndrome-related neural circuits (Celeghin et al., 2023; Bronleigh et al., 2022). Endpoints include longitudinal between- and within-person analyses.

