- When dichotomous (binary) outcome variables: Binary outcomes (e.g., remission, response rates) will be analyzed using logistic regression models, adjusting for baseline characteristics such as age, baseline BMI, and symptom severity. The odds ratios and 95% confidence intervals will be reported.
- When continuous (dimensional) variables (e.g., BMI, BDNF levels, cognitive flexibility) will be analyzed using linear mixed-effects models, and regression models of various types.
- Other: Exploratory Subgroup Analyses:
  Exploratory subgroup analyses will assess treatment effects across different strata (e.g., age groups, baseline severity) using interaction terms in regression models or stratified analyses to explore heterogeneity in treatment responses.
- Other: Sensitivity Analyses:
  Sensitivity analyses will address missing data using methods such as multiple imputation or maximum likelihood estimation. These methods ensure robustness of the findings by accounting for the potential impact of missing data on primary and secondary outcomes.

**Concomitant antidepressant treatment (yes/no; class; dose stability)** will be recorded and may be included as a covariate in exploratory analyses. Sensitivity analyses or subgroup analyses may be performed to explore potential moderating effects on clinical outcomes.

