10.3 Adjustment of Significance and Confidence Interval

A Bonferroni correction or false discovery rate (FDR) adjustment will be applied for multiple comparisons to control Type I error.

Results will be presented with 95% confidence intervals, and significance will be set at a two-tailed p-value of <0.05 after adjustments.

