10.4 Sample Size Calculations

No formal power calculation has been conducted due to the pilot nature of the study. However, 40 participants (20 per group) were chosen based on feasibility and alignment with recommendations for exploratory trials in emerging therapies​.

Post-hoc power analysis will assess the adequacy of the sample size in detecting clinically meaningful changes in primary outcomes.

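### The primary AE/SAE comparison named in section 10.2 does not use the age-group stratum by which randomisation is blocked, so it loses precision if AE rates differ by age group or enrolment period

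*Protocol*

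**What the plan says.** Section 5.1 sets the allocation: "Participants will be randomly assigned (1:1) to either the intervention or control group". It adds: "Block randomization stratified by age group (16–17 and 18–35 years) will ensure balanced representation". The synopsis gives the order and size of the strata: "First 25 participants included above 18 years of age, followed by 15 patients between 16-17 years of age". Section 10.4 gives the total: "40 participants (20 per group) were chosen based on feasibility".

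Section 10.2 then lists what it calls the primary statistical methods for AE/SAE. They are descriptive frequencies, a chi-squared or Fisher test ("Fisher's exact test is preferred for small cell counts (<5"), and "Risk Ratio (RR) or Odds Ratio (OR) with Confidence Intervals". None of these carries the age stratum. Section 10.3 sets the threshold: "significance will be set at a two-tailed p-value of <0.05 after adjustments".

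Elsewhere section 10.2 does use age. The logistic models for response and remission adjust for it, and age group appears in exploratory subgroup analyses. Continuous endpoints "will be analyzed using linear mixed-effects models, and regression models of various types", with no covariates listed. ANCOVA and MANCOVA are allowed when the analysts wish to control for other variables.

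**The concern.** Blocking within strata balances the arms on age group. Any difference in outcome between the age groups therefore drops out of the true sampling variance of the arm comparison. A crude test still leaves that difference in its error term, so its standard error is too large, its interval too wide and its rejection rate under the null below 5%.

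Here the stratum may carry more than age. Minors are enrolled after adults, so age group also marks calendar period and the team's growing experience. Section 8.2 has AEs reported spontaneously by participants or noted by clinicians, in an open-label trial, so reporting could differ between the periods. In a 40-person safety trial, a conservative comparison makes a real excess of AEs in the psilocybin arm easier to miss. The precision lost was already provided by the design.

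This is not a detail left for an analysis plan to fill. The protocol names specific unstratified procedures for its primary endpoint.

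**Working it through.** **Inputs.** From the protocol: 1:1 allocation, 20 per arm, strata of 25 and 15, two-sided 0.05. The protocol gives no AE rates, age effect or block size, so there is no stated figure to reproduce. Assumed: the odd strata split 12/13 and 8/7 (or the reverse) so that each arm has 20, and AE rates are varied over a range. Multiplicity adjustment is left out, so each figure is for one test at 0.05.

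**Large-sample check.** Let pA and pM be the adult and minor AE rates under the null, and p = 0.625·pA + 0.375·pM. The share of outcome variance explained by age group is R² = 0.625·0.375·(pA − pM)² / [p(1 − p)]. The crude test then has size of about 2·[1 − Φ(1.96/√(1 − R²))].

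For 30 v 70%: p = 0.45 and R² = 0.2344·0.16/0.2475 = 0.15, so the size is 2·[1 − Φ(1.96/0.921)] = 3.3%. A risk-difference interval is too wide by a factor of about 1/0.921 = 1.09. For 30 v 60%, R² = 0.087 and the factor is about 1.05. For 40 v 60%, R² = 0.038 and the factor is about 1.02.

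**Exact null size (full enumeration, 20 v 20).** Brackets show the same overall rate with no age effect.

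| Adults v minors | Fisher | Chi-squared | Stratified CMH, no continuity correction |
|---|---|---|---|
| 40 v 60% | 1.9% (2.1%) | 3.9% (4.3%) | 4.6% |
| 30 v 60% | 1.8% (2.3%) | 3.8% (4.7%) | 4.8% |
| 30 v 70% | 1.3% (2.2%) | 3.0% (4.4%) | 4.8% |

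The protocol's rule switches between Fisher and chi-squared, so it lies between those two columns. The bracketed values separate the two causes. For chi-squared, ignoring the stratum costs 0.4, 0.9 and 1.4 points. For Fisher, most of the gap to 5% is there with no age effect at all.

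**Size of the stratified alternatives.** Over 30/30, 45/45, 40/60, 30/60 and 30/70, the exact stratified test has size 3.1–3.5%. Its mid-p version (p-value minus half the probability of the observed result and its ties) has 4.7–5.7%. CMH with continuity correction has only 0.4–2.0% over the wider set of rates tried.

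**Power for a 30-point excess in the psilocybin arm (rates capped at 98%), averaged over the two splits.**

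| Control rates, adults v minors | Fisher | Exact stratified | Chi-squared | Uncorrected CMH |
|---|---|---|---|---|
| 30 v 30% | 35% | 40% | 46% | 46% |
| 45 v 45% | 38% | 41% | 49% | 48% |
| 50 v 50% | 41% | 44% | 53% | 51% |
| 40 v 60% | 39% | 46% | 51% | 51% |
| 30 v 60% | 34% | 46% | 46% | 51% |
| 30 v 70% | 34% | 48% | 46% | 54% |

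At 30 v 70%, chi-squared power is 40% or 52% depending only on which arm receives the odd minor. CMH gives 54% either way.

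**Continuous endpoints.** With an age effect of d SD, the unadjusted interval is wider by about √(1 + 0.2344·d²). At d = 0.5 this is √1.059 = 1.03, and at d = 0.8 it is √1.15 = 1.07. Simulation (200,000 runs) gives 1.03 and 1.07, with t-test sizes of 4.4% and 3.7%. A model with the stratum term holds 4.9–5.0%.

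**The case against.** Four objections have weight.

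- **Discreteness.** A reader might infer that ignoring the strata is what drives the AE tests well below 5%. The calculation does not support that. Fisher sits at 2.0–2.5% for common AE rates with no age effect, and chi-squared loses under one point of level at moderate age gaps. Only a gap of about 40 points brings chi-squared down to 3%.
- **Continuous models.** A reader might also infer that the continuous-endpoint models ignore the strata. The text leaves their covariates open and allows ANCOVA and regression, so age group is neither included nor excluded. An analysis plan could settle this.
- **The age effect is assumed.** Nothing in the protocol says that minors have more or fewer AEs. If age group and enrolment period are not prognostic, the crude intervals are not too wide, and stratifying can cost up to 2 points of power against chi-squared.
- **The exact remedy is itself conservative.** It does not restore 5%, and at 30 v 70% its power (48%) is close to that of chi-squared (46%). At a single split chi-squared can be the higher of the two.

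The error never inflates type I error, and the protocol admits limited power and puts descriptive frequencies first. All of this limits the size of the point. It does not remove it: the named primary methods omit the randomisation factor. Compared like for like, the exact stratified test had more power than Fisher in every case tried. Uncorrected CMH was at least level with chi-squared on average once the age gap reached 20 points.

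**Conclusion.** The concern holds in a limited form. The primary AE/SAE comparison as written does not use the stratum by which participants are randomised. If AE rates differ by age group or enrolment period, it is conservative and less precise than the design allows: chi-squared size is 3.8–3.9% at moderate assumed gaps and 3.0% at 30 v 70%, against 4.6–4.8% for uncorrected CMH. For continuous endpoints the protocol merely fails to commit to the stratum. The cost of leaving it out is an interval about 3% wider at a 0.5 SD age effect and 7% wider at 0.8 SD.

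These sizes rest on assumed AE rates and age effects, and on strata of 25 and 15 from the synopsis. Section 10.5 does not fit those strata: it opens recruitment of minors after 25 adults have been through dosing, whereas 25 randomised adults at 1:1 would put only 12 or 13 in the psilocybin arm, which totals 20. The two passages must be reconciled.

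**What to change.** In section 10.2:

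- Make the primary AE/SAE comparison a Mantel-Haenszel risk ratio or risk difference with 95% CI, stratified by randomisation age group (16–17, 18–35).
- Test it with CMH, stated to be without continuity correction. When cells are small, use the exact stratified test or its mid-p version in place of Fisher, and say which. The exact version stays mildly conservative; the mid-p version can slightly exceed 5%.
- Keep the crude frequencies and percentages as description.
- Name randomisation age group as a fixed effect in the mixed and regression models for continuous endpoints.

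Reconcile the synopsis and section 10.5 on the number of adults and how they are counted.

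The cost is one or two sentences and one degree of freedom in the models. No new data are needed. If age group proves not to be prognostic, the loss against chi-squared is 0–2 points of power. If no minors are enrolled, the stratified analysis reduces to a single-stratum one.

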4.3 Primary Endpoint

- **Safety:** Incidence of adverse events (AEs) and serious adverse events (SAEs) during the trial period.

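### The only effect sizes named for the primary safety endpoint are a risk ratio or an odds ratio; at 20 per arm a risk difference with a score-type interval would be the safer measure

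*Protocol*

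**What the plan says.** Protocol section 4.3 sets the primary endpoint as "Incidence of adverse events (AEs) and serious adverse events (SAEs) during the trial period". Section 5.1 states "Participants will be randomly assigned (1:1) to either the intervention or control group", and section 10.4 states "40 participants (20 per group) were chosen based on feasibility". Section 10.4 also says "No formal power calculation has been conducted due to the pilot nature of the study", so no event rate or target effect is on record.

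Section 10.2 lists several primary methods side by side:

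- "Descriptive Frequencies and Percentages";
- a chi-squared or Fisher comparison of proportions, where "Fisher's exact test is preferred for small cell counts (<5" in a cell;
- the effect size: "Risk Ratio (RR) or Odds Ratio (OR) with Confidence Intervals: Report these measures of effect size to quantify the magnitude and precision".

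One sentence on reading the result follows: "An RR > 1 would indicate a higher risk in the intervention group".

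Section 10.3 adds that results carry 95% confidence intervals and that significance is two-tailed at 0.05 after adjustment. No risk difference is named anywhere in section 10.

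**The concern.** Section 5.1 of the protocol concedes that 40 participants give limited power for between-group differences. The primary result will therefore rest on estimates and their intervals more than on tests, and the effect measure should be one that can be computed and read in any table the trial may produce.

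A ratio does not meet that need in two plausible situations: no serious events under TAU, and almost everyone on psilocybin reporting some event. The protocol itself describes earlier psilocybin studies without serious adverse events (section 3 and the dosing-interval rationale in section 5.1) and calls anxiety during dosing common (section 3).

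The open choice between the two ratios adds a second weakness. In an unblinded trial with common events, the apparent size of the effect depends on which ratio is shown. If the choice is made after the data are seen, a reader cannot tell whether the data influenced it.

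**Working it through.** **Inputs.** n = 20 per arm (section 10.4), allocation 1:1 (section 5.1). Event risks are not in the protocol and are assumed over a range. Arms are treated as independent binomials. The protocol states no rate, power or effect size, so there is no figure of its own to reproduce.

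**Step 1: no events under TAU.** With a zero TAU count the risk ratio is x/0 or 0/0, and the odds ratio likewise. For true risk p the chance is (1 − p)^20. The usual log-scale interval for the risk ratio needs events in both arms. With equal risks it fails with probability 1 − [1 − (1 − p)^20]².

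| Assumed risk, both arms | P(TAU count = 0) | P(a zero in either arm) |
|---|---|---|
| 2% | 0.98^20 = 0.668 | 0.890 |
| 5% | 0.95^20 = 0.358 | 0.588 |
| 10% | 0.90^20 = 0.122 | 0.228 |
| 20% | 0.80^20 = 0.012 | 0.023 |

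**Step 2: every psilocybin participant has an event.** P(20/20) = p^20, which is 0.012 at 80%, 0.122 at 90% and 0.358 at 95%. The psilocybin odds are then 20/0, so the odds ratio is infinite (undefined if TAU is also 20/20). The risk ratio stays finite provided TAU has events. For 20/20 against 14/20:

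- RR = 1/0.70 = 1.43
- SE(log RR) = √(1/20 − 1/20 + 1/14 − 1/20) = √0.0214 = 0.146
- 95% interval = exp(0.357 ± 1.96 × 0.146) = 1.07 to 1.90

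**Step 3: divergence when events are common.** For 18/20 against 10/20, RR = 0.90/0.50 = 1.8 and OR = (18/2)/(10/10) = 9.0. The same table gives two summaries that differ fivefold.

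**Step 4: the alternative in the same kinds of table.** Newcombe's interval combines the Wilson limits (l, u) of each arm: lower = d − √[(p1 − l1)² + (u2 − p2)²], upper = d + √[(u1 − p1)² + (p2 − l2)²].

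Worked for 2/20 against 0/20: Wilson limits are 0.028 to 0.301 and 0 to 0.161, and d = 0.10.

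- Lower = 0.10 − √(0.072² + 0.161²) = −0.077
- Upper = 0.10 + √(0.201² + 0²) = 0.301

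| Psilocybin v TAU | Risk difference, points (95% CI) | RR | OR |
|---|---|---|---|
| 0/20 v 0/20 | 0 (−16.1 to 16.1) | undefined | undefined |
| 2/20 v 0/20 | 10 (−7.7 to 30.1) | infinite | infinite |
| 4/20 v 0/20 | 20 (−0.1 to 41.6) | infinite | infinite |
| 20/20 v 14/20 | 30 (7.7 to 51.9) | 1.43 | infinite |

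The difference and its interval exist in every row.

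**The case against.** The strongest reply is that no primary result would be lost. The frequencies, percentages and Fisher's test are defined in every table, and a risk difference can be read from the percentages. That is correct, and it is why the point is minor. What can fail is the named effect size and its interval.

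Second, zero counts under TAU may be unlikely. Section 9.1 counts any inpatient admission as serious and states no exemption for admissions due to anorexia, re-hospitalisation is a relapse component in section 4.4, and follow-up runs to 12 months. At a 20% risk the chance of no TAU event is about 1%. This stands as a limit on step 1. It does not touch steps 2 and 3. Against it, section 9.1 words the adverse-event definition around subjects given a medicinal product and section 9.3 starts collection at the first dosing, either of which could lower TAU counts.

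Third, exact and score intervals for ratios exist with a zero cell, though one limit can be infinite, and the interval type and zero-cell handling are commonly left to the SAP. This is fair, and the absence of such rules is not counted here. The ratio-only choice and the unsettled pair of ratios are in the protocol text.

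Fourth, section 10.2 speaks of measures in the plural, so both ratios may be reported. That would remove the selection problem, but the text also joins them with an or and should say which is meant.

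A reader might further infer that the sentence on a risk ratio above 1 is a decision rule that often signals harm falsely. The protocol does not support this. The sentence gives the direction of the ratio, it follows directly on a requirement for confidence intervals, and sections 10.2 and 10.3 add a test and a two-tailed threshold. With a 5% risk in both arms psilocybin has the higher count in 34.5% of trials, but a risk difference above 0 would occur in exactly the same trials. This is ordinary sampling, not a false-positive rate, and the share with a finite ratio above 1 is 11.5%.

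**Conclusion.** The point holds at minor severity. The protocol names only ratio measures for its primary endpoint and leaves the choice between them open.

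At 20 per arm neither ratio has a finite estimate when TAU has no events. The chance of this ranges from 67% at an assumed 2% risk to 1% at 20%, and the true TAU risk is unknown. The odds ratio alone fails at 20/20 on psilocybin against fewer under TAU; 20/20 itself has a chance of 12% at a 90% event risk and 36% at 95%. It would be wrong to conclude that the risk ratio is also undefined there: it is finite as long as TAU has events.

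These figures assume independent participants and exactly 20 per arm. The dosed cohort may be somewhat larger, because recruitment continues until at least 20 have been dosed. That would lower the chances slightly without changing the conclusion.

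**What to change.** In section 10.2:

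- Name the risk difference (psilocybin minus TAU) with a Newcombe or Miettinen-Nurminen 95% interval as the effect measure for adverse-event and for serious-adverse-event incidence, beside each arm's proportion with an exact interval.
- Keep the risk ratio as a descriptive figure when both arms have events, and drop the odds ratio for event incidence.
- Reword the sentence on a risk ratio above 1 so that direction is always read together with the interval.
- Leave the planned percentages and Fisher's test as they are.

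The cost is about two lines of analysis text, with no change to data collection or sample size. The downside is that the risk ratio becomes secondary and one more interval is reported.

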9.2 Assessment of Adverse Events

-Events will be assessed by the clinical team for causality, intensity, and seriousness and potential relationship to treatment (psilocybin 25mg).

The investigator is responsible for determining whether there is a causal relationship between the AE/SAE and use of the investigational medicinal product.

Consideration should be given to whether there is a reasonable possibility of establishing a causal relationship between the adverse event and the investigational medicinal product based on the analysis of the available evidence.

All AE can be categorized as either likely related, possibly related, unlikely related or not related, in accordance with the definitions below:

Likely related: Clinical event, including abnormal results from laboratory analyses, occurring within a reasonable time after administration of the intervention/investigational medicinal product. It is unlikely that the event can be attributed to underlying disease or other medications but is most likely caused by the investigational medicinal product and its emergence is reasonable in relationship with use of the investigational medicinal product.

Possibly related: Clinical event, including abnormal results from laboratory analyses, occurring within a reasonable time after administration of the intervention/investigational medicinal product. The event could be explained by the investigational medicinal product and its emergence is reasonable in relationship with use of the investigational medicinal product, but there is insufficient information to determine the relationship. The event could be explained by an underlying disease or other medications.

Unlikely related: Clinical event, including abnormal responses from laboratory tests, unlikely to be related to the intervention/investigational medicinal product and can be reasonably explained by other medication or underlying disease.

Not related: Clinical event, including abnormal results from laboratory analyses, that is not reasonably related to the use of the intervention/investigational medicinal product.

Those AEs which are suspected of having a causal relationship to the investigational medicinal product will be followed up until the subject has recovered or is well taken care of and on the way to good recovery.

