If the reporting investigator does not provide any information on causality, the sponsor should consult with the reporting investigator and encourage the expression of a position on this issue. The sponsor must take into account the assessment of causality provided by the investigator. If the sponsor disagrees with the investigator's assessment of causality, both the investigator's and the sponsor's views should be included in the report.

Each adverse event shall be classified by an investigator as mild, moderate or severe.

Mild: The adverse event is relatively tolerable and transient in its nature but does not affect the subject’s normal life.

Moderate: The adverse event causes deterioration of function but does not affect health. The event can be sufficiently unpleasant and interferes with normal activities but does not completely obstruct them.

Severe: The adverse event causes deterioration of function or work ability or poses a health risk to the subject.

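### The between-arm test of AE relatedness is uninformative because TAU receives no psilocybin, and the severity test does not say how participants without an AE are counted

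*Protocol*

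**What the plan says.** Protocol section 10.2 introduces the primary endpoint analysis as follows: "We will analyse differences in the number of participants and severity experiencing AE/SAE between the groups". It then lists the primary statistical methods: frequencies and percentages; a chi-squared or Fisher test of proportions with a risk ratio or odds ratio; and finally "Comparing Severity and Relatedness is assessed with Mann-Whitney U test or Student t-test to compare severity distributions between groups".

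Other sections bear on that last item:

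- **What relatedness refers to.** Section 9.2: "Events will be assessed by the clinical team for causality, intensity, and seriousness and potential relationship to treatment (psilocybin 25mg)". Section 5.1 gives the control arm TAU only. Section 7.4 lets controls switch to psilocybin after the six-month follow-up, and section 9.3 collects AEs to 12 months, starting at the first dosing.
- **Who judges relatedness.** Section 9.2: "The investigator is responsible for determining whether there is a causal relationship between the AE/SAE and use of the investigational medicinal product". The data list in section 10.2 has "Relatedness to intervention (assessed by safety review committee)".
- **Severity grades.** Section 9.2 grades each event as mild, moderate or severe. Two definitions read "Moderate: The adverse event causes deterioration of function but does not affect health" and "Severe: The adverse event causes deterioration of function or work ability or poses a health risk to the subject".
- **Sample size.** Section 10.4 gives 40 participants, 20 per group, without a formal power calculation, and adds: "Post-hoc power analysis will assess the adequacy of the sample size in detecting clinically meaningful changes in primary outcomes".

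**The concern.** Three features of this primary-endpoint method cause trouble.

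1. **Relatedness.** Before any switch no control has taken psilocybin, so no control AE can properly be attributed to it. The control arm sits at zero because of the design and not because of anything observed. A between-arm test then adds nothing to a description of the dosed arm.
2. **Severity.** Grades attach to events, and a participant without an AE has none. A test restricted to people with an AE selects on something that happens after randomisation. If the drug adds many mild events, the treated arm's average grade among people with an AE falls even though more people are affected.
3. **Choice of test.** Leaving Mann-Whitney or Student's t open on a short ordinal scale, in an open-label trial of 40, lets the p-value depend on which is picked.

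Two lesser faults feed the same analysis. The severity grades overlap, and two sections name different assessors of relatedness. The post-hoc power analysis is then given the job of judging whether the sample was adequate for this endpoint.

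**Working it through.** The protocol states no AE rate, effect size or power, so there is no figure to reproduce. The inputs from the protocol are 20 per arm (10.4), 1:1 allocation (5.1) and two-sided 0.05 after multiplicity adjustment (10.3). The AE counts below are assumptions for illustration.

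**Relatedness, control arm fixed at 0/20.** Section 10.2 names rank and t-tests here. I reduce relatedness to yes/no and use Fisher's test to show the effect of the fixed zero. With equal arms, two-sided p = 2 × C(20,k)/C(40,k).

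| Related, psilocybin vs TAU | Fisher p |
|---|---|
| 4/20 vs 0/20 | 2 × 4,845/91,390 = 0.106 |
| 5/20 vs 0/20 | 2 × 15,504/658,008 = 0.047 |
| 6/20 vs 0/20 | 0.020 |

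The unadjusted threshold is five dosed participants with a related AE. The chance of reaching it is P(X ≥ 5) with X ~ Bin(20, r). It is 37% at r = 20%, 76% at r = 30% and 99% at r = 50%. The result depends only on r in the dosed arm; the control arm contributes no information.

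**Severity, assumed worst grade per participant.**

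| Arm | None | Mild | Moderate | Severe |
|---|---|---|---|---|
| Psilocybin | 2 | 14 | 4 | 0 |
| TAU | 12 | 3 | 4 | 1 |

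- Incidence: 18/20 vs 8/20, Fisher p = 0.002, psilocybin worse.
- Only participants with an AE: mean grade (14×1 + 4×2)/18 = 22/18 = 1.22 vs (3×1 + 4×2 + 1×3)/8 = 14/8 = 1.75. TAU now looks worse. Mann-Whitney p = 0.042 by the normal approximation and about 0.05 by permutation (400,000 draws).
- All 40, with no AE scored 0: 22/20 = 1.10 vs 14/20 = 0.70. Psilocybin is worse. Mann-Whitney p = 0.047 by the normal approximation and about 0.04 by permutation.

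**Choice of test.** For the same 40 values, the sums of squares about the means are 30 − 22²/20 = 5.8 and 28 − 14²/20 = 18.2. The pooled variance is 24.0/38 = 0.632, so t = 0.40/√(0.632 × 2/20) = 1.59 on 38 df and p = 0.12. The two tests that the protocol allows fall on opposite sides of 0.05.

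**How often the direction flips (assumed, 10,000 simulated trials).** Take AE rates of 90% vs 30%. Psilocybin grades are split 75/20/5% mild/moderate/severe and TAU grades 20/50/30%. The AE-only test is significant with TAU worse in 70% of trials, while the all-participant test is significant with psilocybin worse in 73%. If both arms share the mix 60/30/10%, the AE-only test is significant in about 4% of trials (either direction). The reversal therefore needs control AEs that are fewer and more severe.

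**Severity grades.** Loss of function appears in both the Moderate and the Severe definition. The health criterion separates them only in part, because the Severe definition joins its criteria with *or*. An event that impairs function without a health risk fits both.

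**Precision available.** With no events among n dosed participants, the one-sided 95% upper limit is 1 − 0.05^(1/n). For n = 20 this is 1 − 0.05^0.05 = 13.9%.

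**The case against.** The strongest reply is that the primary endpoint is incidence, and section 10.2 puts incidence first, with Fisher's test and a risk ratio or odds ratio. In the example that analysis gives p = 0.002 against psilocybin, so the harm would be seen. This stands. A reader might infer that the primary safety result as a whole could come out reversed, and the protocol does not support that.

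Second, the protocol nowhere says that severity is tested only among people with an AE. The unit of analysis and the handling of participants without an event can be left to an analysis plan. This also stands: the reversal is conditional. The counts are invented, the permutation p of the AE-only comparison sits at the 0.05 line, and section 10.3 requires significance after adjustment. With two tests under Bonferroni the limit is 0.025, and neither severity p-value in the example meets it.

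Third, a reader might call the relatedness test significant by construction. It is not: 4/20 versus 0/20 gives p = 0.106. Nor is it strictly true that controls can never have a related AE, since they may switch after month 6 while AEs are collected to month 12. Such an event would contaminate the randomised comparison and would not make it meaningful.

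What the reply does not reach is the relatedness comparison itself. It is named among the primary methods, and further detail in an analysis plan cannot make it informative. The closing words of that sentence describe severity only, so the relatedness test is also poorly specified.

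**Conclusion.** The point holds in this form. The between-arm comparison of relatedness is uninformative as written, whatever its p-value. This rests on the protocol's own definitions and needs no assumed rates.

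The severity comparison is under-specified. It can point the opposite way from incidence if it is restricted to people with an AE and control AEs are fewer but more severe; it does not do so when no AE is scored as the lowest grade in all participants. The size shown (1.22 vs 1.75 against 1.10 vs 0.70) depends on assumed counts.

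The conflict over the assessor, the overlapping grades and the post-hoc power analysis are genuine but secondary. Power computed at the observed effect is a function of the observed p-value. Section 10.4 states no clinically meaningful difference at which it could be computed otherwise. This should be corrected before the analysis, but it does not invalidate the incidence analysis.

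**What to change.** - **Relatedness:** report it descriptively, in dosed participants only, without a between-arm test. Reconcile sections 9.2 and 10.2 on whether the investigator's or the committee's judgement is analysed.
- **Severity:** compare each randomised participant's worst grade (none, mild, moderate, severe) with an exact or permutation Wilcoxon test. Delete the Student t-test alternative. Stratifying by the randomisation age group is optional.
- **Counting window:** for the between-arm comparison, count AEs only up to any switch. Start from a date that exists in both arms, because the first dosing in section 9.3 does not exist for TAU.
- **Grades:** reword Moderate and Severe in section 9.2 so that an event fits only one.
- **Section 10.4:** replace post-hoc power with exact (Clopper-Pearson) limits for key AEs and SAEs in the dosed cohort, and state that 0/20 leaves a one-sided 95% upper limit of 13.9%.

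The cost is mostly wording in the protocol and analysis plan. The exception is the start date: AE recording for TAU has to be fixed from that date before enrolment proceeds, because missed control AEs may not be recoverable later.
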